# A drug free solution for improving the quality of life of fibromyalgia patients (Fibrepik): study protocol of a multicenter, randomized, controlled effectiveness trial

**DOI:** 10.1186/s13063-022-06693-z

**Published:** 2022-09-05

**Keywords:** Fibromyalgia, Quality of life, Millimeter waves, Endorphins, Pain, Sleep disturbances, Holistic approach

## Abstract

**Background:**

Fibromyalgia is a form of chronic widespread pain that is defined as a syndrome of chronic symptoms of moderate to severe intensity, including diffuse pain, fatigue, sleep disturbance, cognitive impairment, and numerous somatic complaints. To date, there is no specific drug treatment for fibromyalgia but only symptomatic treatments. A drug free solution based on a wristband that emits millimeter waves associated with a therapeutic coaching program was developed. The application of millimeter waves on an innervated area has been described to have a neuromodulating effect, due to endorphin release stimulation and parasympathetic activation. Coaching is carried out to improve the patient’s adherence and to increase compliance and effectiveness of the treatment. Regular use of this solution by fibromyalgia patients is expected to improve sleep quality, reduce anxiety and pain levels, and, at the end, increase the quality of life.

**Methods:**

This trial is performed over 8 French inclusion centers for a total of 170 patients. The effectiveness of the solution is evaluated according to the primary objective, the improvement of the quality of life measured through the dedicated Fibromyalgia Impact Questionnaire after 3 months. Patients are randomized in two groups, Immediate or Delayed. The Immediate group has access to the solution just after randomization in addition to standard care, while Delayed has access to the standard of care and waits for 3 months to have the solution. The purpose of this methodology is to limit deception bias and facilitate inclusion. The solution consists in using the device for three sessions of 30 min per day and four coaching sessions spread over the first 2 months of wristband usage.

**Discussion:**

The objective is to confirm the effect of the integrative approach based on endorphin stimulation and a therapeutic coaching program in nociplastic pain and specifically for the patient suffering from fibromyalgia. If the effectiveness of the solution is demonstrated, we will be able to respond to the demand of fibromyalgia patients for access to an effective non-medicinal treatment to improve their quality of life.

**Trial registration:**

ClinicalTrials.gov NCT05058092

**Supplementary Information:**

The online version contains supplementary material available at 10.1186/s13063-022-06693-z.

## Administrative information

Note: the numbers in curly brackets in this protocol refer to SPIRIT checklist item numbers. The order of the items has been modified to group similar items (see http://www.equator-network.org/reporting-guidelines/spirit-2013-statement-defining-standard-protocol-items-for-clinical-trials/).

## Introduction

### Background and rationale {6a}

Fibromyalgia (FM) is a chronic rheumatic condition with an estimated prevalence between 2 and 6,4% depending on the criteria used in diagnosis [1]. The main symptoms of FM are widespread musculoskeletal pain, stiffness, fatigue, non-restorative sleep, mood disorders, cognitive dysfunction, anxiety, depression, general sensitivity, and physical and emotional inability to carry out normal daily activities [2–4]. Because fibromyalgia is a multifaceted disease in which the pathogenesis is still unclear, no dedicated curative treatment for this disease has been validated. As for most of the nociplastic pain, the main therapeutical strategy is focused on symptom mitigation and quality of life (QoL) improvement. In 2017, the European Alliance of Associations for Rheumatology (EULAR) updated its recommendations for the management of FM based on scientific evidence from high-quality reviews and meta-analyses [5]. In first-line, the EULAR recommended to inform patients by providing therapeutic education and then prescribing non-pharmacological therapies such as aerobic and strengthening exercise that can be combined with other non-drug therapies like cognitive behavioral therapies, acupuncture, hydrotherapy, massage, meditative movement therapies, and mindfulness-based stress reduction [5]. Drug treatments such as opioid analgesics, antidepressants, and anti-epileptics are used as second-line treatments proposed by the EULAR, as they do not always give convincing results and present significant risks for patients. Their prescription is recommended only when patients are in severe pain (duloxetine, pregabalin, tramadol) and/or in case of sleep disturbances (amitriptyline, cyclobenzaprine, pregabalin) [5].

The non-drug therapeutic solution proposed is totally in line with the proposals made by EULAR. It is based on a solution that includes a wristband, a mobile application, and a therapeutic coaching program. The wristband emits millimeter waves (MMW) that stimulate the nerve endings located in the skin [6]. This stimulation induces a series of coordinated physiological actions, which in turn induce the synthesis and release of endogenous opioids (endorphins) that have a hypoalgesic effect [7, 8]. The effectiveness of MMW therapy on different types of pain has been demonstrated in several animal [9–11] and human studies [12–16]. Pre-clinical studies have shown that endogenous opioids play a role in the balance of sympathetic/parasympathetic activities, towards an inhibition of the sympathetic system and an activation of the parasympathetic system [17–20] and thereby participate in the modulation and regulation of stress [21]. The increase in parasympathetic activity also facilitates sleep onset and improves the quality of sleep [22]. Pain and sleep disorders are central symptoms in FM and are intimately linked. Indeed, experimental studies in humans and animals show that there is a relationship between disorders of the sleep-wake cycle and diffuse musculoskeletal pain [23]. A poor night’s sleep is often followed by an increase in pain intensity the next day. Inversely, a particularly painful day is often followed by a bad night [24]. In healthy subjects, sleep deprivation causes hyperalgesic changes [23]. Healthy subjects report symptoms like those reported by people suffering from fibromyalgia (musculoskeletal pain, fatigue, and mood disorders). These symptoms have a strong impact on the quality of life of fibromyalgia patients. Also, the parasympathetic effects of using the wristband would improve the patients' sleep, consequently their pain and overall quality of life.

However, chronic pain could not be addressed by taking into account the only physiological dimension. Chronic pain is a multi-dimension situation, physiological, psychological, and social [25]. It is why most advance clinical research in that field insists on the need to consider each of its dimensions.

In addition to the endorphin stimulation, the coaching program has several objectives. First, it provides therapeutic education about the wristband (mechanism of action, expected effects, technical aspects) to improve adherence and reduce apprehension and side effects. For this purpose, two sessions of coaching are proposed: when the wristband is delivered and after 7 days of start of use. The second objective is to improve compliance and effectiveness. Indeed, a meta-analysis evaluating the effects of ecological interventions (EMI: Ecological Momentary Intervention) based on the use of technological tools (websites, apps) on mental health (stress, anxiety, and depression) shows that the results can be up to 62% greater when the intervention involves the punctual assistance of a health professional compared to an intervention without a health professional [26]. The authors of the study suggest that this assistance could increase users’ motivation and adherence, which in turn could increase the effectiveness of the intervention. To this end, two follow-up phone calls are proposed: one after a month of usage and one after 2 months.

### Objectives {7}

Pre-clinical and clinical data show the hypoalgesic and parasympathetic effects of MMW exposure on healthy participants and patients with pain. By allowing the release of endogenous opioids, the MMW transmitter system could improve the quality of life of fibromyalgia patients, measurable by a decrease in the Fibromyalgia Impact Questionnaire (FIQ) score, and reduce their sleep disorders, observable by a decrease in the Pittsburgh Sleep Quality Index (PSQI) score, between inclusion and 3 months of follow-up.

### Trial design {8}

This multicenter superiority trial is randomized into two parallel groups of the type of “Immediate solution” versus “Delayed solution.” The main interest in that design is to limit the disappointment bias, each group has access to the solution: one immediately on the day of randomization, the second group after 3 months, once the primary objective is assessed. The allocation ratio between the two groups is 1:1.

## Methods: Participants, interventions, and outcomes

### Study setting {9}

The study takes place in France in seven pain centers of academic hospitals and one private neurology practitioner. The list of participating centers is accessible on ClinicalTrials.gov (NCT05058092).

### Eligibility criteria {10}

To be included, patients must meet the following inclusion criteria:Age ≥ 18Diagnostic of fibromyalgia according to the American College of Rheumatology criteria 2016 [27]Fibromyalgia Impact Questionnaire ≥ 39 (moderate and higher forms) on the inclusion day (D0)Wrist size compatible with the deviceHaving access to a smartphone running under Android 8 or iOS 12 or laterAccepting the Fibrepik app on smartphone and counting of their steps by their smartphoneAccepting the installation of the Google Fit app for patients whose smartphone runs on Android (necessary for counting steps)Being affiliated to the French social security system or beneficiary of such a system.

If patients have one of the following exclusion criteria, they cannot be included:Characterized depressive episode according to the French version of the Diagnostic and Statistical Manual of Mental Disorders, Fifth Edition (DSM-5) [28]Substantial change in treatment in the 3 months prior to inclusion and in the months to come: change in analgesic class, introduction of a new treatment, …Chronic inflammatory pathology (chronic inflammatory rheumatism, rheumatoid arthritis, psoriatic arthritis, spondyloarthritis, lupus,...)Person in civil proceedingsHaving a dermatological pathology on the wrists, such as oozing dermatosis, hyper sweat or an unhealed lesionBeing tattooed, pierced of having surgical material implanted on both wristsBeing allergic to metals and/or siliconeReferred to articles L1121-5 to L1121-8 of the French Public Health Code: pregnant, parturient, or nursing woman; person deprived of liberty by the judicial or administrative decision; person subject to a legal protection measure or unable to express his/her consent; person under psychiatric careIn a period of exclusion from other interventional research.

### Who will take informed consent? {26a}

Participants are pre-selected on their medical records within the 8 centers renowned for their implication in fibromyalgia expertise and research. If they meet the eligibility criteria, a Clinical Research Assistant (CRA) contacts these patients by phone to inform them of the study and to verify any criteria that were not in the medical record. If the patient is interested to participate, the trial information letter is sent by post or email. The inclusion visit is scheduled at least 8 days after. During the inclusion visit, the physician gives the patient all the information about the study. If the patient agrees to participate, the patient and the physician sign the consent form.

### Additional consent provisions for collection and use of participant data and biological specimens {26b}

N/A. There is neither biological collection nor ancillary study.

## Interventions

### Explanation for the choice of comparators {6b}

The comparator is conventional medical care because there is no reference treatment in France for fibromyalgia. In addition, following guidelines in chronic nociplastic pain disorder, and specifically in fibromyalgia, we do not plan to propose its wristband alone. Indeed, the coaching allows to transmit knowledge (mechanism of action, expected effects, technical handling) in order to make the patient autonomous in the identification and the implementation of an adequate use of the wristband, i.e., that is, appropriate to them according to the daily evolution of their symptoms. This initial therapeutic information, inspired by Therapeutic Patient Education (TPE) methods, is carried out during a one-hour interview on the day the wristband is handed over, and then reinforced by a phone call 7 days later. Follow-up interviews (45 min by phone) are undergone after one and 2 months of use to help patient self-assess their use of the wristband and the impact on their condition. When necessary, posology (the number of sessions, times at which sessions are scheduled, the intervals between sessions) is revised between patient and coach. These interactions with the patient are indissociable key elements of the solution to improve effectiveness. Coaching is a key point of our study, leading to the impossibility to implement “placebo wristband and placebo coaching.”

### Intervention description {11a}

The Figure 1 presents the intervention into the two study groups.

**Fig. 1 Fig1:**
[figure not shown]
Presentation of the study design

#### Solution description

The solution consists of a wristband, a mobile application, and a coaching program. The wristband is designed to deliver millimeter waves. At the internal part of the band, in contact with the inside of the wrist, two blocks of transmitting antennas and microwave bricks allow to generate the emission of electromagnetic waves of frequency 61.2 GHz with a power density of 13 to 17 mW/cm^2^. A side control button is used to start a session. An indicator light shows that a session is in progress or paused, as well as a possible malfunction. After a session (30 min), the wristband must be recharged by placing it on its charging cradle. Each session is recorded in an internal memory and transferred to the coach via the mobile app.

In this trial, it is recommended that the patient perform at least three sessions per day, including one in the hour before bedtime to facilitate sleep onset and increase sleep quality. Additional sessions may be added if desired.

The Fibrepik application allows the patient to track their sessions and the number of steps taken each day. Through the application, the patient can receive push notifications sent by their coach in case of poor compliance for example. When the patient connects the wristband to the application, usage data is sent to a server, which allows for remote collection of the frequency of use and the distribution of sessions during the day. Access to this data will enrich the understanding of the clinical trial results and are used by the coach, via a secure access, to better adapt their recommendations to each patient during the coaching sessions.

Coaching is key to improve patient adherence to the technology and to increase compliance and effectiveness of the treatment. Coaching is provided by CRA, psychologists, or nurses from each clinical center, specifically trained by a neuropsychologist before the beginning of the inclusions. Four coaching sessions are realized from the delivery of the wristband:At D0 (or M3), upon delivery of the wristband, the patient is trained to use the wristband and the application and is informed about endorphins and their effects in the body. Recommendations for scheduling sessions are made according to the patient’s main symptoms.At D7 (or M3+7 days), a phone call is made to ensure that the patient has no difficulties in using the device, that they have drawn up a routine to use it and to answer questions.At M1 (or M4) and M2 (M5): a phone call, during which an assessment is made of the patient’s usage and impressions of change on their condition. If necessary, the coach provides advice on when and how often to use the wristband.

To standardize the three phone calls, coaches follow dedicated questionnaires that guide the exchange and address the technical aspects, the frequency and habits of use of the patient, the effects felt, ... To evaluate the autonomy of the patient over the following months, coaching does not continue beyond 3 months after patients have started using their wristband.

#### Immediate solution description

The “Immediate solution” group consists of (i) from D0 to M3—3 months with the solution (wristband, Fibrepik App, and coaching) in addition to the standard of care, (ii) from M3 to M6—3 months with the wristband and Fibrepik App in addition to the standard of care, and (iii) from M6 to M9—3 months with the standard of care. These 3 last months with the standard of care is to evaluate the reminiscence effects of the millimeter waves.

#### Delayed solution description

The “Delayed solution” group consists of (i) from D0 to M3—3 months with the standard of care, *ii) from M3 to M6—3 months with the solution add to the standard of care, and (iii) from M6 to M9—3 months with the wristband and Fibrepik App in addition to the standard of care.

To avoid disappointment and lack of investment in the study by the Delayed group, we chose to provide the solution to this group after the collection of the main objective. The fact that these fibromyalgia patients could not benefit from the proposed innovative solution but only continue their usual treatment would have led to many patients refusing to participate or withdrawing consent. Since fibromyalgia is a long-term chronic disease, the 3-month delay for the Delayed solution group to benefit from the solution seems to be a very short period and perfectly acceptable.

### Criteria for discontinuing or modifying allocated interventions {11b}

Patients who could no longer use the wristband because of an adverse effect will stop the treatment. However, they will be followed in the study until the end of their participation. In case of a serious adverse event that no longer allows the patient to participate in the study, the patient’s participation will be stopped. The reason for any discontinuation of treatment or study will be documented and recorded.

### Strategies to improve adherence to interventions {11c}

The coach has access for each patient to the data of the Fibrepik application: the wristband usage data and step counts. If necessary, during the first 3 months of the wristband use, the coach can send a notification to the patient’s smartphone to remind them, for example, to perform sessions or to reinforce the planned coaching sessions scheduled at 7 days (D7) and then after one and 2 months of starting to use the solution. Sending a notification is also used to remind patients in both groups to complete their home follow-up booklet.

### Relevant concomitant care permitted or prohibited during the trial {11d}

All drug treatments or complementary therapies already initiated before the start of the study may be continued but the patient must not have any substantial modification of treatment (change in analgesic class, introduction of a new treatment) during the trial participation. At the end of each week, the patient reports the treatments and complementary therapies taken in their home follow-up booklet.

### Provisions for post-trial care {30}

At the end of the trial, if the patient wishes to continue to use the wristband, they may keep it in addition to conventional care for people with fibromyalgia.

If a serious adverse effect occurs during the trial, the sponsor's insurance would cover the cost of compensation.

### Outcomes {12}

The primary outcome is to compare between the two randomization groups the percentage of patients who significantly improve their fibromyalgia-specific quality of life between the inclusion visit at D0 and the 3-month visit (M3). The fibromyalgia-specific quality of life is evaluated with the French-validated version of the self-questionnaire Fibromyalgia Impact Questionnaire (FIQ). A decrease in FIQ score of 14% or more is considered clinically meaningful [29].

In secondary outcomes number 1 to 5, we compared between the two groups the evolution from D0 to M3 of criteria related to the symptoms of fibromyalgia patients:Questionnaires: Quality of sleep on the Pittsburg Sleep Quality Index (PSQI); Anxiety and depression on the Hospital and Anxiety Depression scale (HAD); Fatigue on the Multidimensional Fatigue Inventory questionnaire (MFI 20); General quality of life on the EQ-5D-5L; Physical activity on the Global Physical Activity Questionnaire (GPAC)Average pain score over the week on a visual analogic scale (VAS)Class, dose, and the number of analgesic, antidepressant, and sleeping pill intake. Patient-reported dose and number of these treatments in his home follow-up bookletConsumption of care in relation to the symptoms of fibromyalgia reported each week by the patient in his home follow-up booklet: care (procedures, medical consultations, hospitalizations); complementary care (acupuncture, osteopath, naturopath, etc.); psycho-behavioral therapies; complementary treatments (phytotherapy, homeopathy, food supplements)Number of steps measured by the subject’s smartphone and collected through the Fibrepik mobile application.

In secondary outcomes 6 to 9, we evaluated:6.Impression of the disease change at M3 by the patient on the Patient Global Impression of Change (PGIC) scale and by the caregiver on the Clinician Global Impression of Change (CGIC) scale7.Solution and wristband objectives: Frequency of use of the wristband on the 6-month period of use it. The frequency of use is an extract of the wristband log file; Usability of the wristband on the modular evaluation of key Components of User Experience (meCUE) questionnaire at M6 for patients of the Immediate solution group and at M9 for patients of the Delayed solution group; Solution satisfaction questionnaire (questionnaire created by the sponsor) at M6 for patients of Immediate solution group and at M9 for patients of Delayed solution group8.Number, description, and classification (serious/non-serious) of adverse effects9.Primary outcome and secondary outcomes 1 to 6 evaluated at 6 and 9 months.

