The Multidimentional Fatigue Inventory is a 20-item scale designed to evaluate five dimensions of fatigue: general fatigue, physical fatigue, reduced motivation, reduced activity, and mental fatigue. The score of each dimension is between 4 and 20. Higher score correspond with more acute levels of fatigue [33].

The EQ-5D-5L is a standardized instrument developed by the Euroquol Group as a measure of health-related quality of life. The EQ-5D-5L contains 5 questions (5Q) on mobility, self-care, usual activities, pain/discomfort, and anxiety/depression with responses rated in 5 levels (5L) and a visual analog scale between 0 and 100. Responses of the 5 questions result to an index [34].

The Global Physical Activity Questionnaire (GPAC) is a questionnaire for the adult population constituted of 16 questions that measure physical and sports activities during a typical week [35]. It aims to collect information on the practice of physical activities (frequency, duration, and intensity of activities) and on sedentary behaviors. The questionnaire covers the following topics: activities at work, during transport, and leisure activities. The results provide a score to classify individuals according to 3 levels of physical activity: low, medium, and high.

The Patient Global Impression of Change and the Clinician Global Impression of Change scales are a 7-point scale depicting a patient's rating of overall improvement [36].

The modular evaluation of key Components of User Experience questionnaire (meCUE) includes 30 items divided into four independent modules: product perception, emotions, consequence of use, and global evaluation. For modules 1 to 3, the user indicates their level of agreement with statements on a 7-point Likert scale, from “strongly disagree” to “strongly agree.” The last question of the meCUE (module 4) asks the user to give an overall evaluation of the product on a scale from − 5 (bad) to + 5 (good) [37].

The solution satisfaction questionnaire (questionnaire created by the sponsor) is a specific questionnaire to the solution including three parts in order to evaluate the patient's satisfaction with the wristband, the mobile application, and the coaching program. A global score between 0 and 100 is given for each part and qualitative questions allow us to better understand this global score.

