## Statistical methods

### Statistical methods for primary and secondary outcomes {20a}

Descriptive analyses will be expressed by means − standard deviations and medians − interquartiles for quantitative data, as well as numbers and percentages for qualitative data.

The analysis of the primary endpoint will be performed using a Fisher exact test. For secondary endpoints at M3, all endpoints evaluating a change in score between D0 and M3 will be analyzed via bivariate linear regressions, considering the randomization group and the value of the score at D0. Qualitative criteria will be analyzed using a Fisher test. The secondary endpoint 8 is descriptive and will follow indications for descriptive analysis. For secondary endpoint 9, since analysis considers several measurement points with different states, mixed regressions (linear or logistic depending on the type of variable) will be implemented. Data at M6 from the delayed intervention group will be analyzed for comparison at M3 via a McNemars test (test of proportions for paired data).

These analyses are planned in two stages: (i) all criteria evaluated at 3 months will be performed when all patients have made their follow-up visit at M3 and (ii) all criteria evaluated at 6 and 9 months will be analyzed when the follow-ups at M9 of all patients are completed.

The results will be presented in accordance with the recommendations of the CONSORT Statement. These analyses will be implemented after a consistency check and a freeze of the database, in accordance with the good practices of the Grenoble Alps University Hospital. The software used will be Stata 15 or a more recent version (StataCorp LLC).

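### FIQ is analysed only as a 14% responder, so no mean FIQ difference is planned at M3; the ordered PGIC and CGIC scales are left to a test that ignores order

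*Protocol article*

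**What the plan says.** **Objective.** Objectives {7} expects a gain in quality of life "measurable by a decrease in the Fibromyalgia Impact Questionnaire (FIQ) score" between inclusion and 3 months.

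**FIQ in the outcomes.** Under Outcomes {12} the primary outcome is the percentage of patients who improve from D0 to M3, with this threshold: "A decrease in FIQ score of 14% or more is considered clinically meaningful". The secondary list opens: "In secondary outcomes number 1 to 5, we compared between the two groups the evolution from D0 to M3 of criteria related to the symptoms". It names PSQI, HAD, MFI-20, EQ-5D-5L, GPAC, pain VAS, drug intake, care consumption and steps, but not FIQ. Outcome 6 is "Impression of the disease change at M3 by the patient on the Patient Global Impression of Change (PGIC) scale", with the CGIC beside it. Outcome 9 is "Primary outcome and secondary outcomes 1 to 6 evaluated at 6 and 9 months", so at M6 and M9 FIQ is again the responder percentage.

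**Methods.** Statistical methods {20a} gives the primary endpoint a Fisher exact test. Secondary endpoints that are changes in score from D0 to M3 get a linear regression on group and the D0 score. For the rest: "Qualitative criteria will be analyzed using a Fisher test".

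**PGIC and CGIC.** Plans for assessment and collection of outcomes {18a} says that they "are a 7-point scale depicting a" rating of overall improvement. A footnote to Table 1 says that they are not collected at D0.

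**The concern.** A responder comparison says how many patients crossed a threshold. It does not say by how much FIQ moved, and it depends on patients close to a 14% fall. As listed, the trial would give a baseline-adjusted mean effect for sleep, anxiety and fatigue but none for the instrument that carries its objective. A mean FIQ difference added once results are known would be post hoc.

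For PGIC and CGIC, a Fisher test on seven categories treats any reordering of those categories as the same data. A consistent shift towards improvement then counts for no more than an unpatterned difference.

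**Working it through.** **1. The plan's own figure.** Inputs from Sample size {14}: 50% versus 25%, alpha 5%, power 90%. Sidedness is not stated; two-sided is used here. With pooled variance, p̄ = 0.375:

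n = [1.960·√(2·0.375·0.625) + 1.2816·√(0.5·0.5 + 0.25·0.75)]² / 0.25² = 76.7, so 77 per group.

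This matches the stated figure. By exact enumeration, the planned Fisher test has 87.6% power at 77 per group and 90.1% at the 85 per group to be recruited.

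**2. The same effect on the score scale.** The article gives no SD, so assume a normal change score with equal SDs in both groups. The shift that yields 50% and 25% responders is

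d = z(0.50) − z(0.25) = 0 + 0.6745 = 0.674 SD.

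Normal approximation: n = 2·(1.960 + 1.2816)² / 0.6745² = 46.2, so 47 per group. With the t distribution it is 47.2, so 48 per group.

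**3. Power at 77 per group, control rate 25%.**

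| True Immediate rate | Shift (SD) | Score, t-test | Responder, Fisher |
|---|---|---|---|
| 50% | 0.674 | 98.6% | 87.6% |
| 45% | 0.549 | 92% | 70% |
| 40% | 0.421 | 74% | 45% |
| 35% | 0.289 | 43% | 22% |

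**4. Adjustment for D0.** If D0 FIQ has correlation r with the analysed change, the variance shrinks by 1 − r². Using 46.2·(1 − r²):

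- r = 0.3 gives 42.0, so 43 per group
- r = 0.5 gives 34.6, so 35 per group
- r = 0.6 gives 29.6, so 30 per group

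The values of r are assumptions.

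**5. Which M3 rule fits PGIC and CGIC.** Statistical methods {20a} has two rules for secondary endpoints at M3. The regression needs a D0 value, and these scales have none. That leaves the Fisher rule for qualitative criteria.

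**6. Size of the loss on a 7-point scale.** Simulation with 77 per group, 1,500 runs, and an assumed control distribution of 3, 7, 15, 35, 20, 13 and 7%, with the other group shifted on a latent normal scale:

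| Latent shift (SD) | Unordered Fisher (2×7) | Wilcoxon | Gain in points |
|---|---|---|---|
| 0.3 | 20% | 40% | 19 |
| 0.4 | 36% | 66% | 30 |
| 0.5 | 55% | 84% | 29 |
| 0.6 | 75% | 94% | 19 |

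Gains are taken from the unrounded values.

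**The case against.** The best defence is that nothing listed is invalid. A fall of at least 14% is itself a decrease in FIQ, so the primary does not contradict the objective. The threshold is cited and prespecified, and the sample size is right for it. Supportive analyses are often placed in an analysis plan, which is not shown. All of this stands, and it limits the point to an addition. It does not remove the point, because the article gives an explicit, numbered list of endpoints and the FIQ score is not on it.

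Four stronger readings are tempting, and the article does not support them:

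- *The responder primary is wrong or underpowered.* It is neither. It has about 88% to 90% power under its own assumptions.
- *The article assigns Fisher to PGIC and CGIC.* It names no test for them. Fisher is reached by elimination, and an analysis plan could name an ordinal test or a grouping.
- *GPAC level is also tested without its D0 value.* Outcomes {12} lists GPAC among the questionnaires compared from D0 to M3, and section {18a} says that it yields a score. It can therefore be read as a change score with D0 adjustment, although the same passage also describes three levels.
- *CGIC is the only blinded rating, so its test matters most.* Outcomes {12} says that the caregiver makes this rating. Physicians are blinded and coaches are not, and no passage says which of them completes the CGIC.

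**Conclusion.** The point holds as a gap in the endpoint list and an inefficient default test, not as an error in the primary analysis. FIQ appears only as a responder at M3, M6 and M9, and no mean FIQ difference is planned.

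Under the protocol's own rates, a score comparison would need 48 per group instead of 77. At 77 per group it has 98.6% power against 87.6%. The gap widens if the effect is smaller: about 74% against 45% at 40% versus 25%. These figures rest on a normal change score with equal SDs. They are also illustrative because the 14% threshold is relative to D0, whereas the proposed endpoint is the score adjusted for D0.

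The PGIC and CGIC part rests on inference about which rule applies. Its size, roughly 20 to 30 points of power, rests on an assumed category distribution. If Fisher is not intended, the article gives these scales no fitting M3 method, and the same remedy applies.

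**What to change.** - Keep the 14% responder as the primary endpoint, with its sample size unchanged.
- Name the M3 FIQ total score as a secondary endpoint. Analyse it by linear regression on group and D0 FIQ, with centre as an optional covariate, and report the mean difference with its 95% CI.
- Name a Wilcoxon test or a proportional-odds model for PGIC and CGIC at M3 in place of the Fisher test.

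The cost is a few lines of text and a small number of models. Table 1 already schedules FIQ at D0 and M3, and PGIC and CGIC at M3, so no patient or visit is added. Both changes should be dated before the M3 data are analysed. If that analysis has already been run, the additions should be reported as post hoc.
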